This trial aims to fill the gaps in the current evidence base by evaluating the delivery, impact, acceptability and cost-effectiveness of a community based exercise programme (FaME) and a home based exercise programme (OEP) supported by similarly aged (peer) mentors, compared with usual care for primary care patients. The underlying assumption is that the exercises will produce sufficient subjective well-being and improved mobility to encourage continuation of higher levels of physical activity after the cessation of the intervention. Each exercise programme will be compared with usual care for effectiveness in producing sustained change in physical activity. The two programmes will be compared for cost-effectiveness if both are effective in promoting sustained change in physical activity. The primary hypotheses are: 1) Both exercise programmes produce sustained changes in physical activity (PA) compared with usual care, and 2) The Otago programme (OEP) is more cost effective than FaME

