## Objectives

The primary objective is to determine the effect of two evidence based exercise programmes designed for older people, compared with usual care (i.e. with no special interventions to promote physical activity) on the achievement of recommended physical activity targets 12 months after cessation of intervention.

The secondary objectives are to:

(1) determine the health benefits of the programmes to participants starting at various levels of physical activity, particularly the effects on physical and psychological status, health status, health-related quality of life and quality adjusted life years (QALYs).

(2) estimate the costs of the exercise interventions, and possible cost offsets, and to assess the cost-effectiveness of community group exercise, and home-supported exercise compared with each other, and with usual care.

(3) determine the acceptability of the programmes, adherence rates, enabling factors and barriers to future implementation.

(4) compare the time course of responses by participants in terms of exercising at the recommended levels, at 0, 6, 12, 18 and 24 months after cessation of the intervention, between those undergoing the exercise programmes, and those receiving usual care.

(5) determine participants' perceptions of the value of exercise, and the predictors of continued exercise.

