### Sample size

Sample size estimates are based on the numbers of participants needed to detect differences in proportions of participants in intervention and control groups:

1) Participating in physical activity (defined as reaching the national target recommendations of five sessions of 30 minutes or more of at least moderate activity per week).

2) Self perceived health as measured by the EQ-5D index, from which meanQALY scores and the incremental cost-effectiveness ratio will be calculated.

Under individual randomisation, sample size calculations for a small effect size (0.3) [61] equivalent to a mean difference of 0.05 in the EQ-5D index in general community samples requires 176 participants per study group [62]. Published evidence of participants in a cluster randomised trial of physical activity promotion showed the proportions of participants achieving the same recommended targets for physical activity to be 14.6% (intervention subjects) vs. 4.9% (control subjects) [63]. A total of 215 participants in each study group are required to detect this difference between study groups with 90% power (5% 2-sided significance). Current plans seek a 1% increase in the number of people achieving the physical activity target of five sessions of 30 minutes or more of at least moderate activity per week, year on year [1].

Data from 24 general practices in the British Regional Heart study suggested that an intra-class correlation coefficient (ICC) not exceeding 0.02 was appropriate for physical activity outcomes among middle aged men, but this study aimed to represent the full range of cardiovascular disease prevalence across Britain and the range would probably be less in the proposed study as it is less geographically dispersed [64]. Also ICCs collected for a range of variables in primary care settings have typically averaged 0.01 [65].

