Based on an intra class correlation coefficient of 0.01 the design effect would be 1.31, because 32 participants will provide data per practice (see next paragraph). If 215 participants per arm are required (before allowing for attrition) for an individually randomised design (90% power, 5% 2-sided significance), 282 per arm would be required for the clustered design. Allowing for 30% attrition, this equates to 403 per arm. The sample size is based on detecting differences between each intervention (exercise programme) and the control arm, and there is unlikely to be enough power to detect modest differences in outcome between the two intervention arms.

Assuming an average practice size of 6000 patients, 15% (900) of whom are aged 65 and over [66] and a random 1 in 2 sample (ratio will vary according to the practice size) of patients are approached to take part in the study, 600 patients aged 65 and over would be approached. Assuming that approximately 45 of these patients per practice agree to participate, and allowing for an attrition rate of 30%, outcome data would be obtained on 32 participants per practice.

It is expected that all or most patients in each practice will be invited to join the trial. In larger than average practices, however where the patient list is very large, a stratified random sample of 600 patients will be drawn. Response rates from each practice will be recorded.

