The economic analysis will adopt standard techniques of economic appraisal [72]. The measure of effectiveness will be mean differences in QALY scores at the end of follow up after adjustment for baseline values, estimated in an analysis of covariance. If statistically significant differences between groups are found, incremental cost effectiveness ratios will be calculated to show the extra cost incurred per QALY gained. Comparisons will be conducted between the usual care group and each type of exercise programme, and between the two interventions, using group means of follow-up QALY values after adjusting for baseline levels. The impact of uncertainties in the estimation of costs and outcome variables will be explored using one way and probabilistic sensitivity analysis. Bootstrap methods will be used to represent uncertainty of estimates, either for constructing confidence intervals or probability curves.

Sensitivity analyses will investigate the cost-effectiveness of the interventions for people with different levels of physical activity, health status and health related quality of life at baseline. Secondary cost-effectiveness analyses will be conducted using physical activity and other outcomes as the measures of effectiveness.

Missing outcome data will be assumed to be "missing at random" (MAR), conditional on key predictors of "missingness" (in particular baseline values of the response variable, treatment arm, and measures of compliance post randomisation) Multiple imputation of outcome variables will be carried out using these predictors of "missingness" [73]. A further sensitivity analysis will be carried out where all who do not report their exercise levels will be assumed to be non-exercisers.

The full analysis set will comprise all randomised participants for whom one post-baseline assessment of the primary outcome measure is available. The per-protocol set will comprise all randomised participants who are deemed to have no protocol violations. CACE analysis will be carried out [74].); this seeks to estimate the difference between compliers in the intervention groups with those who would have complied in the non-intervention group. The safety set will be all randomised participants who undertake at least one OEP session or FaME class.

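### ICERs are calculated only after a significant difference between groups, so no joint cost-effect analysis is assured for OEP versus FaME if their QALYs are similar

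*Protocol article*

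**What the plan says.** Four parts of the protocol article bear on this.

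- **Statistical methods, economic analysis.** Effectiveness is defined first: "The measure of effectiveness will be mean differences in QALY scores at the end of follow up after adjustment for baseline values". The next sentence sets the condition: "If statistically significant differences between groups are found, incremental cost effectiveness ratios will be calculated to show the extra cost incurred per QALY gained". Comparisons of each programme with usual care, and of the two programmes with each other, are then promised "using group means of follow-up QALY values after adjusting for baseline levels". One-way and probabilistic sensitivity analysis and bootstrap intervals or probability curves follow, with no condition attached.
- **Background.** The second of two primary hypotheses is: "The Otago programme (OEP) is more cost effective than FaME". A different condition appears just before it: "The two programmes will be compared for cost-effectiveness if both are effective in promoting sustained change in physical activity".
- **Objectives.** Secondary objective 2 is "to assess the cost-effectiveness of community group exercise, and home-supported exercise compared with each other, and with usual care", with no condition.
- **Sample size.** The trial is sized for each programme against usual care, and the article concedes that "there is unlikely to be enough power to detect modest differences in outcome between the two intervention arms".

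**The concern.** A programme can be the more cost-effective one because it does more good, because it costs less, or through some mix of the two. A test on QALYs alone looks at one axis only. If OEP and FaME produce nearly the same QALYs and OEP is cheaper, the second hypothesis is true, yet the QALY test should be non-significant and the rule as written produces no ICER.

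The rule also selects. With a small true difference, a significant result occurs only when the estimate is well above the truth, so an ICER that is reported rests on an overstated QALY difference.

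What is at stake is whether a hypothesis listed as primary has an assured analysis. The physical activity endpoint is not affected.

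**Working it through.** **Inputs from the protocol article (Sample size)**

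- Physical activity: 14.6% against 4.9%, 90% power, two-sided 5%, 215 per group.
- ICC 0.01, 32 participants with data per practice, design effect 1.31, 282 analysed per arm, 403 recruited per arm after 30% attrition.
- EQ-5D: "small effect size (0.3) [61] equivalent to a mean difference of 0.05 in the EQ-5D index", 176 per group.

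**Reproducing the stated figures**

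- The two-proportion formula gives 195 per group without a continuity correction and 215 with it, as stated.
- Design effect: 1 + (32 − 1) × 0.01 = 1.31. Then 215 × 1.31 = 281.7, so 282. Then 282 / 0.70 = 402.9, so 403.
- EQ-5D: a t-based calculation at effect size 0.3 needs 175.4, so 176, at 80% power. The article does not state the power for this figure; 90% would need about 235.

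**Assumptions for the OEP versus FaME test**

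- The SD implied by the EQ-5D inputs, 0.05 / 0.3 = 0.167, applies to the QALY measure. The article gives no SD for QALYs.
- The significance test is two-sided at 5%. The article gives no level for the QALY test.
- The condition is applied pair by pair.
- Effective sample size per arm is 282 / 1.31 = 215.3.

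**Chance that the condition is met**

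SE = 0.167 × √(2 / 215.3) = 0.0161. For a true difference d, the probability is Φ(d/SE − 1.96) + Φ(−d/SE − 1.96). With a baseline correlation r, the SE is multiplied by √(1 − r²). The article plans an analysis of covariance but gives no r, so 0.5 and 0.7 are assumed values.

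| True QALY difference | No covariate gain | r = 0.5 | r = 0.7 |
|---|---|---|---|
| 0 | 5% | 5% | 5% |
| 0.017 (0.1 SD) | 18% | 22% | 31% |
| 0.025 (0.15 SD) | 34% | 43.5% | 59% |
| 0.05 (0.3 SD) | 87.5% | 95% | 99% |

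- Without covariate gain the chance is one half at about 1.96 × 0.0161 = 0.032.
- The difference detectable with 80% power is (1.96 + 0.84) × 0.0161 = 0.045.
- At an ICC of 0.02, the upper value the article discusses, the effective size is 282 / 1.62 = 174.1 and the 0.025 figure falls from 34% to 29%.

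**Size of the selection effect**

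At a true difference of 0.1 SD (0.0167), the mean absolute estimate among significant results is 0.241 SD (0.040), a ratio of 2.4. With r = 0.5 or 0.7 the ratio is 2.1 or 1.8. At a true difference of 0.05 it is about 1.1, so the distortion matters only when the true difference is small.

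**Setting the conditions side by side**

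| Place | Condition on comparing the two programmes |
|---|---|
| Background | Both programmes effective on physical activity |
| Objectives, secondary objective 2 | None |
| Statistical methods, ICER | Statistically significant differences between groups |
| Statistical methods, pairwise QALY comparison | None |

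**The case against.** The strongest reply is that the condition governs one product, the ICER, and that much else is unconditional. The section on ascertainment of outcomes commits to costing delivery of both programmes and to comparing health and social care costs between the exercise groups and with usual care. Statistical methods adds pairwise QALY comparisons, probabilistic sensitivity analysis, bootstrap curves and secondary analyses on other outcomes. With near-equal QALYs a ratio is unstable anyway, and separate cost and QALY results would say more. This largely stands. A reader might infer that the second hypothesis cannot be answered at all; the text does not support that. It leaves unsaid whether cost and effect are analysed jointly when the QALY test is not significant.

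Other points also limit the concern:

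- **Frequency.** A reader might infer that the ICER will usually be missing. That holds only for true differences below about 0.03, and below a smaller value if baseline adjustment helps. At 0.05, the one EQ-5D effect the article names, the condition is met 87.5% of the time or more at an ICC of 0.01. The concession on power concerns modest differences in outcome generally, not QALYs specifically.
- **Primary status.** Background calls the hypothesis primary, but Objectives places the comparison among the secondary ones and Statistical methods defines the primary analysis as each programme against control.
- **The Background condition.** Comparing the programmes only if both work is a defensible hierarchy. It needs reconciling with the other passages but is not an error in itself. The article does not say that effective means p < 0.05, so no pass rate can be attached to it.
- **Direction of bias.** An overstated QALY gain makes the ICER too low only when the incremental cost is positive. If the programme with more QALYs is also cheaper, the ratio is negative and has no such reading.
- **End-of-follow-up QALYs.** One could read the effect measure as a value at a single time, so that a gain which fades would be lost. The wording may equally mean QALYs accrued by then, and an article may leave their construction to the full plan. This is not part of the finding.

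**Conclusion.** The concern holds for the significance condition itself. Followed as written, it withholds the ICER for OEP versus FaME about 95% of the time when QALYs are truly equal and about 66% of the time at a true difference of 0.025 (41% to 56.5% if baseline adjustment works at the assumed correlations). It withholds it only 12.5% of the time, or less with baseline adjustment, at 0.05. When the true difference is near 0.017, QALY differences that pass are overstated by roughly 1.8 to 2.4 times on average.

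These sizes rest on carrying an EQ-5D SD of 0.167 over to QALYs, an ICC of 0.01, a two-sided 5% level, pairwise use of the condition and, for the ranges, baseline correlations of 0.5 to 0.7. The logical point needs none of them: a rule that looks at effect alone cannot decide whether a joint cost-effect estimate is worth making.

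The consequence is a hypothesis without an assured joint analysis, alongside passages that set different conditions. It does not extend to the physical activity endpoint, the sample size or data collection.

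**What to change.** 1. Delete the significance condition on the ICER in Statistical methods.
2. For all three pairwise comparisons, report incremental cost, incremental QALYs, and ICER or incremental net monetary benefit, whatever the p-value. Give bootstrap uncertainty from resampling that respects practice clustering, and acceptability curves.
3. Assess the second hypothesis on the incremental net benefit of OEP versus FaME, which stays well behaved when the QALY difference is near zero.
4. Reconcile the both-effective condition in Background with secondary objective 2 and with the pairwise comparisons in Statistical methods. If the hierarchy is kept, say what effective means and which conclusions it restricts, and still report the estimates.

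The cost is revised wording and a few extra tables. No new data are needed and the sample size does not change.

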### Outcome measures

The primary and secondary outcome measures have been chosen to reflect the needs of participants (e.g. functional outcomes, falls, confidence, quality of life, participant costs), of commissioners of exercise services in primary care and policy makers (e.g. physical activity, falls, NHS costs).

The primary outcome will be the proportion reaching the recommended physical activity (PA) target of at least 30 minutes of activity of moderate intensity on at least 5 days each week, measured using the CHAMPS, PASE and PHONE_FITT questionnaires. While measures will be taken at 0, 6, 12, 18 and 24 months after the intervention, our primary analysis will be of 12 month data, as this is the time when the effect of the intervention is expected to be maximal, as seen in a previous evaluation of the OEP in New Zealand [37].

The secondary outcomes will include:

(1) The direct health benefits: i.e. functional and psychological status, the rate of falls (the major safety outcome measure), the number and nature of falls, and fear of falling,

(2) Stage of change, self-efficacy for exercise and physical self-perception (self-esteem relative to the physical domain), which includes measurement of perceived importance (the degree to which participants value their physical condition, body image and physical strength) to inform predictors of exercise adherence and continuation, and participants' judgement of the value or importance of physical activity,

(3) Health - related quality of life and Quality adjusted life years (QALYs) [38],

(4) The NHS and private (participant) costs of each exercise programme, and possible cost offsets, identified from a comparison of health and social service utilisation of participants in all groups during the study period.

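### The predictors named for multiple imputation omit the participant's own activity at the other follow-ups, above all 0 and 6 months, so the 12-month effect may be biased in either direction

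*Protocol article*

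**What the plan says.** All on missing data is in the Protocol article, Statistical methods. Missing outcomes are taken to be missing at random given certain key predictors, "in particular baseline values of the response variable, treatment arm, and measures of compliance post randomisation". The next sentence fixes the method: "Multiple imputation of outcome variables will be carried out using these predictors". One sensitivity analysis follows, in which "all who do not report their exercise levels will be assumed to be non-exercisers". The full analysis set is "all randomised participants for whom one post-baseline assessment of the primary outcome measure is available".

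The Outcome measures section says: "While measures will be taken at 0, 6, 12, 18 and 24 months after the intervention, our primary analysis will be of 12 month data". The primary endpoint is analysed with a logistic random-effects model, and a separate repeated-measures analysis by generalised estimating equations covers all time points. The Sample size section plans for substantial loss: "Allowing for 30% attrition, this equates to 403 per arm".

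**The concern.** The trial asks whether activity is sustained a year after the programmes end. The drop-out to worry about is therefore that of people who lapse and then stop returning questionnaires. Their activity at 0 or 6 months is the most direct evidence on this, and it is collected but not named among the predictors. Under the named list, a person seen to have lapsed at 6 months and missing at 12 months is imputed like a person still active at 6 months with the same arm, baseline value and compliance.

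Compliance does not fill the gap. It is recorded for the 24-week programmes (participants' own record of days in OEP, an instructor's register in FaME), whereas the lapse of interest comes afterwards. Usual care is offered neither programme, so the variable does not exist there.

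The definition of the full analysis set sharpens the point. Everyone in it without a 12-month value has at least one observed post-baseline activity value, and the named list makes no use of it.

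**Working it through.** **The plan's own figures.** For 14.6% v 4.9%, 90% power and 5% two-sided significance, the continuity-corrected formula gives 215 per arm. The design effect is 1 + 31 × 0.01 = 1.31; 215 × 1.31 = 281.65, so 282; 282 / 0.70 = 402.9, so 403. All reproduce, and this point does not affect them.

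**Inputs for the bias check.** From the protocol: 12-month rates p of 14.6% v 4.9% (taken as the truth: difference 9.7 points, odds ratio 3.32) and 30% loss, taken here as loss at 12 months. Assumed, because the protocol gives no figures: 20% (exercise) and 6% (usual care) at target at 6 months, and 60% of those still at target at 12 months.

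**Formulas.** Let q be the share active at 6 months, and d1 and d0 the loss among the active and inactive.
- 12-month rate among those inactive at 6 months: b = (p − 0.6q)/(1 − q). Exercise: (0.146 − 0.120)/0.80 = 0.0325. Usual care: (0.049 − 0.036)/0.94 = 0.0138.
- Large-sample rate when imputing by arm without 6-month activity: [q(1 − d1)0.6 + (1 − q)(1 − d0)b] / [q(1 − d1) + (1 − q)(1 − d0)].

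Example, activity-related loss in the exercise arm only (d1 = 10%, d0 = 35%, total 30%): (0.2 × 0.90 × 0.6 + 0.8 × 0.65 × 0.0325)/0.70 = 0.1249/0.70 = 17.8%. Usual care stays at 4.9%. The difference is 12.9 points and the odds ratio 4.22.

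| Assumed loss pattern | Imputed rates | Difference (points) | Odds ratio |
|---|---|---|---|
| Unrelated to activity | 14.6% v 4.9% | 9.7 | 3.32 |
| Same rates in both arms: active 15%, inactive 33% | 16.9% v 5.8% | 11.1 | 3.32 |
| Active 15% in both arms, total held at 30% | 17.0% v 5.7% | 11.4 | 3.43 |
| Active 10% in exercise arm only | 17.8% v 4.9% | 12.9 | 4.22 |
| Active 10% in usual care only | 14.6% v 5.9% | 8.7 | 2.72 |
| Active 45% in both arms, total held at 30% | 12.2% v 4.1% | 8.0 | 3.20 |

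**Does adding 6-month activity help?** Multiple imputation was simulated with 403 per arm, 20 imputations, 1,500 runs and no clustering. The estimated differences without and then with 6-month activity were: active loss 15% in both arms, 11.3 and 9.65 points; exercise arm only, 12.8 and 9.6; usual care only, 8.7 and 9.7; unrelated loss, 9.7 and 9.7.

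**With baseline and compliance kept in.** The table conditions on arm alone, so it is not the named list itself. A second simulation (1,000,000 per arm) imputed from baseline, arm and compliance. It assumed latent correlations of 0.6 to 0.8 between 6 and 12 months and 0.5 with baseline, with loss of 10–20% in the active and 32–33% in the others. With this pattern in both arms it gave 15.2–16.5% v 5.1–5.6%. That is 4–13% too high on the difference, but the odds ratio is (0.152/0.848)/(0.051/0.949) = 3.34 at the lower end and 3.33 at the upper. With the pattern in the exercise arm only and 4.9% in usual care, the difference is 10.3–11.6 points (6–20% too high) and the odds ratio 3.48–3.84. Some bias therefore remains with the named list under arm-specific loss. Adding the 6-month value brought the estimate back to 9.6–9.7 points.

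**The non-exerciser analysis.** With 30% unrelated loss in each arm it gives 0.7 × 14.6 = 10.2% v 0.7 × 4.9 = 3.4%: 6.8 points, odds ratio 3.20. With exercise-arm-only loss it gives 12.5% v 3.4%, odds ratio 4.02. With usual-care-only loss it gives 10.2% v 4.1%, odds ratio 2.64. The last two remain far from 3.32.

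**The case against.** The strongest answer is that the list is not closed. The three items are introduced as the main examples, nothing excludes the 0- and 6-month values, and a full imputation specification usually belongs in the analysis plan, which is not shown. That stands against any statement that the protocol rules these values out. It does not remove the point: the text marks those three as the important predictors and says imputation uses them, and for sustained activity that is a poor choice.

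A reader might infer that the 12-month effect is overstated. The documents do not support that. They give no drop-out rates by activity, and the direction follows from whichever pattern is assumed. When loss rates by activity are the same in both arms, the risk difference rises but the odds ratio, the scale of the planned logistic model, is almost unchanged.

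Nor are lapsed drop-outs simply imputed as typical of their arm, since baseline activity and compliance also enter. The 18- and 24-month values cannot help for people who leave for good before 12 months; they help only with intermittent missingness. The protocol does not say that compliance enters a single pooled model, or that the repeated-measures analysis uses imputed data, so neither can be held against it.

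The non-exerciser analysis does address people who lapsed and were lost, and it pulls the risk difference down. It is a crude bound, and it does not correct the odds ratio when loss depends on activity differently by arm.

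**Conclusion.** The point holds as a weakness in the stated imputation model. Observed activity at the other follow-ups, above all 0 and 6 months, should be named as a predictor, and compliance cannot replace it. If drop-out depends on interim activity differently by arm, the 12-month effect may be biased up or down. Under the assumed patterns the difference runs from 8.0 to 12.9 points against 9.7, and the odds ratio from 2.72 to 4.22 against 3.32. Those ranges rest on assumed 6-month activity, persistence and loss rates, and on imputation by arm alone; baseline and compliance would be expected to absorb part of the bias. Under equal loss rates by activity the odds ratio is about unchanged. A conclusion that the effect is overstated would go beyond the documents.

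**What to change.** In Statistical methods, replace the predictor list with wording such as: imputation will be done separately by treatment arm; it will include observed activity at baseline and at 0, 6, 12, 18 and 24 months after the intervention, together with the minimisation variables; it will allow for practice; and compliance will be used in the OEP and FaME arms only. Keep the non-exerciser analysis and describe it as a bound.

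The cost is a wording change and a larger imputation model, with no new data. With few participants at target at some visits, the model may need penalisation, or imputation on the continuous activity score followed by derivation of the target.

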## Design/Methods

A 3 arm parallel design cluster controlled trial using minimisation for allocation at the level of general practice in two centres (London and Nottingham/Derby), comparing community-centre based group exercise programme (FaME), with a home based exercise programme and walking plan (OEP) and with usual care. There will be two years' follow-up to determine the impact, acceptability and adherence to the programme, longer term continuation of exercise and cost-effectiveness. The CONSORT diagram [35] summarises the design (Fig 1).

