### Statistical methods

Characteristics of participants and practices will be compared descriptively at baseline. Comparisons between treatment arms will be made using random effects models to allow for clustering between practices. Linear regression models will be used for continuous outcome variables, logistic models for binary outcome variables (in particular the primary endpoint, namely attainment of recommended exercise level at 12 months after the intervention), and Poisson or negative binomial models for data on rate of falls. The assumptions for using each model will be checked and analyses adjusted accordingly. All analyses will be undertaken, adjusted (a) for variables used for minimisation (centre, deprivation and practice size), (b) for baseline values of the outcome measure, and (c) for baseline variables which differ to a clinically significant extent between groups. Differential effects of the intervention by age, sex and baseline activity levels will be assessed for the primary outcome measures by adding terms for the interaction between age, sex and baseline activity levels and treatment arm to the regression models.

Multilevel models will be applied to take account of clustering at the practice level (applicable to all arms of the study) and practitioner effects which will apply to differing extents in the OEP arm (due to the effectiveness of different PSIs) and FaME arm (due to the effectiveness of different PMs). Analyses as recommended by Roberts [70] and Walwyn and Roberts [71] (2009) will be applied for this purpose.

While the primary endpoint will be attainment of recommended exercise levels at 12 months, we will investigate the profile of exercise attainment at all time points (0, 6, 12, 18 and 24 months post intervention). We will carry out repeated measures analysis using generalised estimating equations which account for the intra-participant dependency of the repeated measures. In particular we will investigate evidence for differences in effect of the interventions at the different time points.

As the study consists of two intervention arms and one control arm, primary analysis will consist of comparing each intervention group with the control group. No formal adjustment of p-values will be made, since the sample size has been specifically designed to test each intervention separately.

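### The named imputation predictors omit practice and the minimisation variables, so imputation done as written would give somewhat too narrow intervals despite a random-effects analysis model

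*Protocol article*

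**What the plan says.** Allocation is by practice: Design/Methods describes a "cluster controlled trial using minimisation for allocation at the level of general practice in two centres". Statistical methods carries this into the analysis: "Comparisons between treatment arms will be made using random effects models to allow for clustering between practices". It also says that all analyses will be adjusted for the minimisation variables, for the baseline value of the outcome, and for baseline variables that differ to a clinically important extent.

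The missing-data paragraph of the same section assumes missingness at random given key predictors, "in particular baseline values of the response variable, treatment arm, and measures of compliance post randomisation". It continues: "Multiple imputation of outcome variables will be carried out using these predictors of 'missingness". Neither sentence mentions practice, centre, deprivation or practice size, or says whether the imputation is single-level or multilevel.

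The next sentence reads: "A further sensitivity analysis will be carried out where all who do not report their exercise levels will be assumed to be non-exercisers". The analysis set is then defined: "The full analysis set will comprise all randomised participants for whom one post-baseline assessment of the primary outcome measure is available". No sentence says whether the imputed analysis is the primary one.

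**The concern.** An imputation model should hold at least what the analysis model holds. Here the predictors named for imputation are fewer than the terms in the analysis. If values are drawn from arm, baseline and compliance alone, two imputed people from one practice resemble each other little more than people from different practices in that arm. The random-effects model fitted afterwards sees a weaker practice correlation than the real one and corrects too little. Having practice in the analysis model does not cure this, because the correlation was lost when the data were filled in.

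At stake are intervals that are too narrow and a false positive rate somewhat above the nominal two-sided 5%, in whichever analysis uses the imputed data.

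**Working it through.** **Inputs from the Sample size section.** Rates 14.6% and 4.9%; 90% power; two-sided 5%; ICC 0.01, with 0.02 quoted as an upper figure; about 45 recruited and 32 providing data per practice; 30% attrition.

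**The plan's own figures.** The two-proportion formula gives 195 per group without, and 215 with, a continuity correction; 215 is the stated figure. Design effect: 1 + (32 − 1) × 0.01 = 1.31, as stated ("Based on an intra class correlation coefficient of 0.01 the design effect would be 1.31"). Then 215 × 1.31 = 281.65, or 282, and 282 / 0.7 = 402.9, or 403 per arm. All reproduce. Practices per arm: 403 / 45 = 8.96, so 9.

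**Large-sample check.** Take 45 recruited per practice, a fraction f missing at random within arm, and imputation by arm with no covariates. Variances are in units of outcome variance divided by the number recruited per arm.

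- True variance of the estimate, which rests on the observed people: V = [1 + (45(1 − f) − 1) × ICC] / (1 − f).
- Within-imputation variance: W = 1 + 44 × ICC × (1 − f)². Only pairs in which both people were observed keep the practice correlation; at f = 0.3 that is 0.7 × 0.7 = 0.49 of pairs.
- Between-imputation variance: B = f / (1 − f).
- Estimated over true standard error: √[(W + B) / V].

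| f | ICC | V | W | B | W + B | SE ratio |
|---|---|---|---|---|---|---|
| 0.3 | 0.01 | 1.305 / 0.7 = 1.864 | 1 + 44 × 0.01 × 0.49 = 1.216 | 0.429 | 1.644 | 0.94 |
| 0.3 | 0.02 | 1.610 / 0.7 = 2.300 | 1 + 44 × 0.02 × 0.49 = 1.431 | 0.429 | 1.860 | 0.90 |
| 0.1 | 0.01 | 1.395 / 0.9 = 1.550 | 1 + 44 × 0.01 × 0.81 = 1.356 | 0.111 | 1.468 | 0.97 |

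**Simulation.** Beta-binomial practices, 9 per arm with 45 recruited in each, 30% missing, 20 imputations drawn by arm only, Rubin's rules and a practice-level variance.

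- SE ratio, imputation by arm only: 0.92-0.95 at ICC 0.01; 0.89-0.90 at ICC 0.02.
- SE ratio, observed data only with clustering: 0.98-1.01. The shortfall therefore comes from the imputation.
- False positive rate, imputation by arm only, t on 16 degrees of freedom (18 practices − 2): about 5-6% at ICC 0.01; 6-7% at ICC 0.02.
- SE ratio when each practice is imputed from its own data (practice as a fixed effect): about 1.16-1.21, which is too large.

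The cut-off matters. With |z| > 1.96 and only 18 practices, even the observed-data analysis rejects 6.3-7.2% of the time at ICC 0.01, against 7.0-7.9% with arm-only imputation. Most of that excess over 5% comes from the normal cut-off.

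**The case against.** The strongest reply is that the article never says practice is left out. The list of predictors is introduced as highlighting some of them, not as complete. The analysis is firmly multilevel, and the form of the imputation model is commonly left to an analysis plan, which is not available here. This stands in part: outright exclusion of practice is an inference. But the article is not silent, because it names predictors and says that the imputation will use them. Someone following that text would build a model without practice.

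A reader might also infer that the primary confidence intervals are affected. The documents do not establish this. The zero-exercise analysis is called a further sensitivity analysis, which suggests that the imputation may itself be one. Against that, the full analysis set needs only one post-baseline assessment, so it can include people with no 12-month value. They enter a 12-month model only if that value is imputed. The role is open.

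Three further limits stand:

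- Baseline activity and compliance can differ between practices and would carry part of the practice effect into the imputed values.
- The 30% is a planning allowance. If imputation is confined to the full analysis set, fewer values may be imputed.
- Larger effects, such as a standard error about 17% too small, need an ICC of 0.05. That figure is not in the documents, which plan for 0.01 and cite 0.02 as an upper figure.

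**Conclusion.** The point holds in conditional form. If the named predictors are the imputation model, intervals from the imputed analysis are too narrow. With 30% missing, the standard error is about 5-8% too small at the planned ICC of 0.01 and about 10% too small at 0.02. With 10% imputed at ICC 0.01, the shortfall is about 1-3%. With t on 16 degrees of freedom, the false positive rate is about 5-6% and 6-7% at the two ICCs. These figures assume 9 equal practices of 45 per arm, data missing at random within arm and no covariates in the imputation, so they are upper bounds for the stated predictors.

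The effect is modest at the planned ICC, and its direction is anti-conservative. The documents do not support saying that practice is definitely excluded, that imputed values share no practice effect at all, or that the primary comparison is necessarily the one affected. The correction is still worth making because it costs so little.

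**What to change.** In the missing-data paragraph of Statistical methods, state three things:

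1. Imputation will be multilevel, with a random effect for practice.
2. The imputation model will include centre, deprivation, practice size and the other covariates of the analysis model, besides the predictors already named.
3. Whether the imputed analysis is primary or a sensitivity analysis.

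Practice as a fixed effect should not stand in for the random effect: it makes the standard error about 16-21% too large and so costs power.

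The change is to wording only, with no extra participants or data. Intervals from the imputed analysis become slightly wider, and the imputation takes a little more computing.
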